#### Normalizing retinal subsensitivity might also be mechanistic of LT

Reduced retinal sensitivity to light in winter is associated with SAD [26]. The melanopsin pathway, from the retina to the brain, is an initial input pathway that could lead to downstream changes in circadian entrainment [20], duration of nocturnal melatonin release [27], and seasonal variation in monoamine concentration [28]. In a diathesis-stress model of SAD, low winter light conditions may combine with a genetic diathesis (photopigment genetic variation) to cause melanopsin-driven retinal subsensitivity, leading to an insufficient central nervous system (CNS) signal to either properly entrain the circadian clock, or for non-circadian, direct effects of light on the CNS [29]. A reduced post-illumination pupil response (PIPR) [26, 30], i.e., a smaller net difference in pupil response to red vs. blue light reflex trials, is an established biomarker of melanopsin-driven retinal subsensitivity. Melanopsin-containing retinal cells are uniquely sensitive to blue light, leading to a sustained pupillary constriction when stimulated. The PIPR is a sustained pupillary constriction after lights off and has been linked to melanopsin cell firing through intracellular recording in primates, even when inputs from rods and cones are pharmacologically blocked [30]. The PIPR provides an elegant way to isolate melanopsin contributions from those of rods and cones, making the PIPR a viable candiate biomarker of LT’s target and effect. In a comparison of individuals with SAD and controls with no history of depression tested in winter and summer, the SAD group had a lower PIPR in winter than in summer, whereas controls did not differ across the seasons [31]. In addition, the SAD group had a lower PIPR than controls in winter, but the groups did not differ in summer.

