#### Screening and enrollment procedures

Participants will be recruited from media advertisements, referrals from local physicians and mental health clinics, and community outreach. Interested volunteers will undergo a brief phone screening to assess basic inclusion/exclusion criteria, including assessment of major depressive episode criteria for the previous winter. Those who appear eligible will be invited to review the informed consent form, and if they consent to the study, to proceed with diagnostic interview, the Structured Clinical Interview for DSM-5 Axis I Disorders—Research Version (SCID-5-RV) [41], administered by the P.I. or a trained clinical psychology graduate student research assistant. If the SCID diagnosis is Major Depressive Disorder, Recurrent, with Seasonal Pattern (inclusion criterion a) and there are no comorbid disorder exclusions (exclusion criteria b and c); the participant will be asked to attend the medical screening/work-up where they will undergo a physical examination and medical chart/history review with a physician assistant, vital signs are collected (blood pressure, pulse, height, and weight), and blood is drawn for thyroid panel (TSH, and free T4). If no medical exclusion is identified (inclusion criterion d and no documented evidence of exclusion criteria b, c, or f on the basis of medical record review), the participant enters the symptom monitoring phase of the study. The SIGH-SAD will be administered by a trained research assistant every other week until SIGH-SAD criteria for a current SAD episode (inclusion criterion b) are met. When a potential participant meets SIGH-SAD criteria for a current SAD episode, they will be asked to attend the pre-treatment assessment, at the conclusion of which, the participant is actively enrolled and randomized. After the first week of February, SIGH-SADs will be discontinued for any potential participant not meeting threshold for a SAD episode because: (1) in our experience, after this date, there is low likelihood of developing a full threshold episode in that winter, and (2) insufficient time remains to ensure completion of the pre-treatment assessment procedures and the 6-week treatment phase before the possibility of spontaneous springtime remission.

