### Intervention description {11a}

#### Timing of the treatments

Given SAD’s inherent seasonality, recruitment will begin September 1 and participants will be enrolled on a continuous basis as they qualify. The second week of February will be the latest treatment start date. Similar timing procedures worked successfully in our prior studies. Our data suggest that the treatment groups grew at comparable rates over time with no significant differences in the timing of treatment initiation or cessation between the groups, and that treatments were completed during the winter.

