#### Light therapy (LT)

Participants attend an initial instructional session that follows a script to explain the treatment rationale and assembly/position of the light box. These will be conducted by the (unblinded) P.I. in small groups of 2–4 subjects for efficiency. Effective fall/winter of 2020–2021, the P.I. posted a video recording of the instructional session on the lab’s private YouTube channel for those randomized to light therapy to watch remotely, due to the COVID-19 pandemic. In their homes, LT participants will use the SunRay (SunBox Company, Gaithersburg, MD), a standard device (23” × 15½”× 3¼”) with an ultraviolet shield that emits 10,000-lux of cool-white fluorescent light to the retina when the user is within 18 inches. Each of the 6 weeks, participants will complete the Light Therapy Side Effects Questionnaire used in our prior studies to assess the presence and severity of any side effects attributed to LT and self-reported times for onset of sleepiness, onset/offset of actual sleep, and desired times for onset/offset of sleep over the previous week. Side effects associated with LT are generally mild and can include headache (19%), eyestrain (17%), and feeling “wired” (14%) [46]. Although individuals typically respond within 4 weeks of initiating LT or not at all [16], our LT protocol will be maintained for 6 weeks to match CBT-SAD’s duration. To circumvent ethical concerns of discontinuing LT during the winter (when relapse is likely) [1], participants are encouraged to keep using the light box and bring it to the lab for servicing in May (to check the bulbs against a photometer and download adherence data). In an effort to reduce access to a suitable device as a potential confound, we will offer access to our light boxes to LT participants in winters 2 and 3 and to CBT-SAD participants crossed into LT in winter 2 for use in winter 3.

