##### Winter 2 and 3 follow-up procedures

Follow-up assessments will occur in January of the next two winters (in winters 2 and 3). Testing in January reflects when the vast majority of SAD patients are in episode and when there are sufficient weeks left in the winter to treat them with the alternate modality if we detect a recurrence (i.e., 100% of SAD patients had an annual pattern of depression onset between September and January, 0% remitted before January, and only 22% remitted in January or February) [1]. Consistent with intent-to-treat principles, we will attempt to collect data on all enrolled subjects, including dropouts and those withdrawn from protocol. Participants will be interviewed by a clinical graduate student blind rater with the SIGH-SAD and the SCID-5-RV mood disorders module to assess for a major depressive episode in the interval from treatment endpoint to winter 2 and from winter 2 to winter 3. Participants will be assessed on biomarkers, questionnaire outcomes (BDI-II, BAI, Q-LES-Q, SDS, and MOS-SF-20), and the questionnaires we used in our prior studies to assess treatment utilization in the interim.

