To examine mechanistic differences between CBT-SAD and LT, mixed effects linear regression with subject as a random effect will be used to model biomarker changes during treatment as a function of time, treatment, and their interaction. We will also model the relationship between biomarker change and change depressive symptoms as a function of treatment by letting the regression coefficient differ between CBT-SAD and LT. This will provide a test of whether potential mediators of effect are treatment-specific. The predictive value of biomarkers at baseline, their pre-post treatment change, and the persistence of the change at follow-up will be examined using logistic regression (for post-treatment remission and winter 2 recurrence) and linear regression (for SIGH-SAD and BDI-II scores) with post-treatment and winter 2 outcomes as dependent variables. Interactions between the biomarkers and treatment will be used to test if the associations with outcomes differ in the CBT-SAD and LT groups. Adherence will be included in ancillary analyses to test its effect on the relationships of treatment with biomarkers and LT or CBT-SAD outcomes. The relationships between biomarkers and outcomes will be validated by examining how well they predict post-treatment and winter 3 outcomes for subjects who experience a recurrence at winter 2 and are switched to the alternative treatment. Data from the cross-over subjects will also be analyzed using mixed linear regression to compare within-person differences in pre-treatment biomarkers and their changes during their initial and subsequent treatments. Treatment, time point (winter 1 or 2), and their interaction will be included to test the effect of treatment sequence on within-person differences in biomarker responses to CBT-SAD and LT.

##### Aim 3

Logistic and linear regressions similar to those for Aim 1 will be used to compare the effect of switching from CBT-SAD➔LT versus LT➔CBT-SAD on winter 3 recurrence and depression scores. Post hoc adjustment for any differences between switch groups in baseline characteristics, treatment response, and biomarker profiles will be done by including them as covariates. Mixed linear regression will be used to longitudinally model depression scores over the three winters, with treatment as a time-varying covariate.

##### Aim 4

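### The biomarker–symptom, prediction and mediation models (Aims 2 and 4) name no term for calendar date or day length, so season can confound a path that randomisation does not protect

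*Protocol article*

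**What the plan says.** Timing of the treatments states that "recruitment will begin September 1 and participants will be enrolled on a continuous basis as they qualify" and that "The second week of February will be the latest treatment start date". Both arms are treated for six weeks; for light therapy, "our LT protocol will be maintained for 6 weeks".

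Data analysis, Aim 2, sets out three kinds of model. A mixed model will "model biomarker changes during treatment as a function of time, treatment, and their interaction". Next, "We will also model the relationship between biomarker change and change depressive symptoms as a function of treatment", with the slope allowed to differ between arms. Logistic and linear regressions then predict remission, recurrence and depression scores from the biomarker at baseline, its change over treatment and the persistence of that change. A within-person analysis of crossed-over participants includes treatment, winter (1 or 2) and their interaction. Aim 4 uses parallel process latent growth curves, one biomarker per model, to estimate the path from treatment through biomarker change to symptom change.

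The time-related covariates named elsewhere are wake time for the PIPR, and time of testing with chronotype or melatonin onset for the word task. All concern time of day or the person's own clock. The additional-analyses section offers sex, age, race, ethnicity and number of prior episodes as examples.

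On season, the introduction reports that "the SAD group had a lower PIPR in winter than in summer", while controls did not differ. The screening section stops symptom monitoring in early February so that treatment can finish "before the possibility of spontaneous springtime remission". The follow-up section cites data in which no patient remitted before January and 22% remitted in January or February. It places both follow-ups in January.

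**The concern.** Two participants in the same arm can be in the same study week under opposite seasonal conditions. One who starts in October is treated while days shorten. One who starts in February is treated while days lengthen and natural remission has begun in some patients. If day length affects both the biomarker and the symptoms, the two changes will be correlated across participants even when neither causes the other.

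Biomarker change and symptom change both arise after randomisation. Random allocation makes the arms alike in start date, but it does nothing for the association between those two changes. That association is what the Aim 2 slope estimates and what the mediator-to-outcome path of Aim 4 relies on. At stake is whether a biomarker is called a mechanism of treatment when it partly tracks the calendar.

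**Working it through.** **The plan's own figure.** The sample size section claims 80% power for a biomarker difference of 0.45 SD with 80 per arm. With two-sided alpha 0.05 (assumed), 0.45 × √(80/2) = 2.846, and Φ(2.846 − 1.96) = 0.81. The figure reproduces. This 0.45 SD is used below as the real treatment effect on the biomarker.

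**Calendar window.** The latest start is 8–14 February. Adding 42 days gives an end on 22–28 March in a non-leap year. The article gives no earliest treatment start, only 1 September for recruitment. Mid-October is assumed here.

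**Day-length change over six weeks.** Latitude φ = 44.5° N is assumed. Declination on day *d* of the year is δ = −23.44° × cos(2π(*d* + 10)/365), and day length is (24/π) × arccos(−tan φ × tan δ).

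| Start | Change over 42 days |
|---|---|
| mid-October | −1.7 h |
| mid-November | −0.6 h |
| mid-December | +0.7 h |
| 10 January | +1.6 h |
| mid-February | +2.1 h |

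The sign reverses within the permitted window, and the span is about 3.8 h.

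**Effect on the slope.** Let day-length change explain a share *s* of the variance of both changes, with no true biomarker effect on symptoms. The spurious correlation is √*s* × √*s* = *s*. With 160 participants and treatment in the model, the Fisher approximation gives a test statistic centred at atanh(*s*) × √156:

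- *s* = 0.05: 0.050 × 12.49 = 0.63, rejection about 10%
- *s* = 0.10: 0.100 × 12.49 = 1.25, rejection about 24%
- *s* = 0.20: 0.203 × 12.49 = 2.53, rejection about 72%

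Simulation (2,000 trials per setting, 80 per arm, starts uniform from mid-October to mid-February) gave 8–9%, 25% and 72%. Within one arm of 80 the rates are about 7%, 14% and 43%.

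**Effect on mediation.** A mediator is declared when both the treatment-to-biomarker and the biomarker-to-symptom tests are significant. With a true 0.45 SD treatment effect on the biomarker, the first test succeeds about 81% of the time. The false-mediation rate is therefore roughly 0.81 times the slope's error rate; for example, 0.816 × 0.245 = 0.20.

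| Assumed share *s* | No day-length term | With day-length term |
|---|---|---|
| 0% | 4% | 4% |
| 5% | 7% | 4% |
| 10% | 20% | 4% |
| 20% | 58% | 4% |

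**What is not affected.** With no treatment effect on the biomarker, the test of treatment on biomarker change rejected about 5% of the time at every share. The treatment-by-biomarker interaction rejected about 4–5%. Without a real treatment effect on the biomarker, false mediation stayed at or below 5% with no adjustment.

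**The case against.** **Covariates may be left to a fuller document.** This is a condensed article, its covariate list is given as examples, and a fuller plan may name date. That is fair, and the point is not that a detail is missing. The article states its model terms and its time-related covariates, and a less biased model can replace the stated one at almost no cost.

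**The randomised comparisons are sound.** A reader might infer that season distorts the biomarker comparison between arms. It does not. Allocation is concurrent and 1:1, and start and stop dates were similar between arms in the earlier studies. The time-by-treatment contrast is unbiased in expectation. Season common to both arms also does not create false treatment-specificity.

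**The evidence for season is narrow.** A reader might infer that season is known to drive all the candidate mediators. The article supports seasonality for PIPR and for symptoms only. It gives no size and no evidence of change within the October–March window. It reports nothing of the kind for gamma-band EEG or word-evoked pupil dilation.

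**The error rates follow from assumed shares.** This is correct. They show sensitivity and do not estimate what will happen. At a 5% share the harm is small.

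**The design already limits the problem.** The February cut-off aims to finish before spring. January follow-ups hold those dates nearly constant, so the exposure in Aim 4 comes mainly from winter 1. The winter 1 or 2 term in the cross-over model absorbs an average shift between winters. It does not absorb person-to-person variation in winter 1 start date.

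**Conclusion.** The point holds in limited form and should be acted on. The models exposed are the biomarker-change to symptom-change model, the prediction of outcome from biomarker change, and the mediator-to-outcome path of the growth-curve model. In these, season can be a shared cause, most plausibly for PIPR. A false mediator also requires that treatment really moves the biomarker.

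The documents do not fix the size. It ranges from slight (7% against 4% false mediation at a 5% seasonal share) to serious (58% against 4% at 20%). The calculation assumes latitude 44.5° N, uniform starts from mid-October to mid-February, equal shares for both changes, and two-sided 5% tests. The documents do not support concluding that mediation findings from this trial will be seasonal artefacts. They support only that the stated models cannot separate the two explanations. Aim 1, the sample size and the stated power are unaffected.

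**What to change.** - **Mediation (Aim 4):** enter day length, or calendar date, at each assessment as a time-varying covariate of both the biomarker and the symptom process.
- **Biomarker–symptom and prediction models (Aim 2):** add the change in day length over treatment, or calendar date. Give PIPR priority, since it is the biomarker for which the article itself reports seasonality.
- **Cross-over within-person comparison:** add the winter 1 treatment start date.
- **Randomised contrasts:** the time-by-treatment and treatment-by-biomarker tests need no correction for bias.

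The data management section already has the administration date of each instrument recorded, so the covariate can be derived without new data. The cost is wording in the analysis plan and one or two degrees of freedom per model.

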### Sample size {14}

With a target *N* = 160 (80 subjects in each of the two treatments), the study will have 80% power to detect main effect differences of 22% (e.g., 28% vs. 50%) in winter 2 recurrence, which we expect at a naturalistic follow-up [14, 44]. Sample sizes for comparisons of winter 3 recurrence will depend on the number of recurrences at winter 2. Based on the recurrence rates observed in our prior study, we project that there will be about 37 recurrences in the LT group and 22 recurrences in the CBT-SAD group. This will provide 80% power to detect a difference in winter 3 recurrence of 35% (e.g., 60% vs. 25%) between CBT-SAD➔LT and LT➔CBT-SAD and a difference of 27% (e.g., 23% vs. 50%) between CBT-SAD and LT subjects without winter 2 recurrence. For biomarker comparisons, there will be 80% power to detect differences of 0.45 standard deviation (SD) in post-treatment values or in pre-post treatment changes between CBT-SAD and LT. Power for detecting relationships between biomarkers and outcomes were based on the odds ratio associated with an increase of 1 SD in the biomarker value or its change. For post-treatment remission, there will be 80% power to detect an OR of 2.2 in the CBT-SAD or LT group and a 2.4-fold difference in the ORs for the two treatments. For winter 2 recurrence, there will be 80% power to detect an OR of 2.2 in the LT group, an OR of 2.8 in the CBT-SAD group, and a 2.9-fold difference in their ORs. There was minimal attrition (4.5%) in our previous study, and we anticipate similar retention in this study. However, with attrition as high as 20%, there will be 80% power to detect a difference in winter 2 recurrence of 24% between CBT-SAD and LT and a difference of 39% in winter 3 recurrence between the two switch groups. Empirical sample size estimates^21^ indicate that the study will have at least 80% power to detect a mediated effect if the regression coefficient for the direct effect of treatment after adjustment for the mediator is at least .39 and the coefficients for the effect of treatment on the mediator and the effect of the mediator on outcome after adjustment for treatment are at least .26.

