## Assignment of interventions: allocation

### Sequence generation {16a}

Participants will be randomly allocated to one of the two equal-probability conditions on a continuous basis as they qualify. Project biostatistician/co-investigator (P.M.V.) will design the schedule based on permuted random-size blocks of 4 and 8, stratified by three variables: [1] sex at birth, [2] comorbid diagnosis with two levels (present/absent), and [3] antidepressant medication status with two levels (on medication or not).

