## Data collection and management

### Plans for assessment and collection of outcomes {18a}

#### Biomarker assessments

Pupillary and EEG data will be collected at pre-, mid-, and post-treatment in winter 1; at winter 2 follow-up (and for those who recur and are switched to the alternate treatment modality, again at mid- and post-treatment in winter 2); and at winter 3 follow-up (for all subjects, regardless of recurrence or switch status). The schedule for PAD is the same, with the exception of mid-treatment, due to subject burden and DLMO expense.

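### The Aim 2 biomarker model gives each randomised arm its own baseline mean, so it compares raw changes and loses power that adjusting for the collected baseline would recover

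*Protocol article*

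**What the plan says.** Under Statistical methods {20a}, Aim 2, the between-arm biomarker comparison is a "mixed effects linear regression with subject as a random effect", used to "model biomarker changes during treatment as a function of time, treatment, and their interaction". The section names no pre-treatment biomarker covariate and no common baseline mean.

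Sample size {14} states "80% power to detect differences of 0.45 standard deviation (SD) in post-treatment values or in pre-post treatment changes between CBT-SAD and LT", with "80 subjects in each of the two treatments". Neither scale uses baseline as a covariate.

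The baseline values are collected. Under Biomarker assessments, "Pupillary and EEG data will be collected at pre-, mid-, and post-treatment in winter 1". Phase angle difference follows the same schedule without the mid-treatment visit. Randomisation comes at the end of the pre-treatment assessment (Screening and enrollment procedures), with equal probability and stratified by sex at birth, comorbid diagnosis and antidepressant status (Sequence generation {16a}).

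Covariates for biomarker analyses are named elsewhere: wake time for the post-illumination pupil response, time of testing and chronotype or DLMO for the word task, and sex, age and similar variables in secondary analyses. The pre-treatment value of the biomarker itself is not among them.

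**The concern.** The pre-treatment biomarker is measured before allocation, so any difference between the arms at that visit is chance. A model with a treatment main effect estimates that difference freely and subtracts it in full from the post-treatment difference. The right amount to subtract is only the part that baseline predicts, which is a fraction ρ when the variances are equal. Subtracting all of it adds noise. In any one trial, a chance imbalance at baseline, followed by regression to the mean, shows up as differential change.

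This is not long-run bias. Over repeated randomisations the estimator is centred correctly and the type I error holds. What is lost is precision in the comparison by which the trial judges whether each treatment engages its intended target, which is one of the two stated goals under Objectives {7}.

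**Working it through.** **Inputs.** 80 per arm and 0.45 SD come from Sample size {14}. The model terms come from Aim 2. Assumed, because the protocol gives neither for this comparison: two-sided α = 0.05, and ρ from 0.3 to 0.8. Equal variances before and after treatment and complete pairs are also assumed.

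**1. The protocol's figure.** In the normal approximation, n per arm = 2(1.96 + 0.8416)²/0.45² = 77.5, so 78. With 80 per arm, power is 81.2% (normal) or 80.8% (noncentral t). The detectable difference is 0.443 SD (normal) or 0.446 SD (t). The stated 0.45 SD reproduces as an unadjusted two-sample comparison.

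**2. What the stated model estimates.** Mixed models with time, treatment, their interaction and a random intercept were fitted to simulated complete data. The interaction at post-treatment equalled the raw difference in mean change to numerical precision, both with categorical time and with linear time over three equally spaced visits. If the protocol instead means change scores as the response, the contrast is again unadjusted change.

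**3. Variances, with σ² the variance at one visit.**
- Raw change: 2σ²(1−ρ)
- Conditional on baseline: σ²(1−ρ²)
- Ratio, adjusted to raw: (1−ρ²)/[2(1−ρ)] = (1+ρ)/2, which does not exceed 1

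**4. Power for 0.45 SD of change.** The effective standardised difference after adjustment is 0.45/√[(1+ρ)/2]. At ρ = 0.5 this is 0.45/√0.75 = 0.520. Power is by noncentral t; n per arm is by the normal approximation.

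| ρ | Variance ratio | Power, raw change | Power, adjusted | n per arm for 80% power, adjusted (raw: 78) |
|---|---|---|---|---|
| 0.3 | 0.65 | 80.8% | 93.9% | 51 |
| 0.5 | 0.75 | 80.8% | 90.4% | 59 |
| 0.7 | 0.85 | 80.8% | 86.6% | 66 |
| 0.8 | 0.90 | 80.8% | 84.7% | 70 |

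The detectable difference at 80% power (normal) falls from 0.443 to 0.357, 0.384, 0.408 and 0.420 SD of change.

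**5. Power for 0.45 SD of post-treatment values.** The effective difference is 0.45/√(1−ρ²). Unadjusted power is 80.8%. Adjusted power is 84.3% at ρ = 0.3 and 90.4% at ρ = 0.5. The two scales coincide only at ρ = 0.5. Below that, raw change does worse than ignoring baseline: at ρ = 0.3 a difference of 0.45 SD in values has 67% power by raw change, 81% by post-treatment values alone and 84% with adjustment.

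**6. Simulation check.** In 3,000 trials at each ρ, power for raw change against ANCOVA was 80.9% vs 92.7% (ρ = 0.3), 80.7% vs 90.0% (0.5) and 81.8% vs 87.3% (0.7). Variance ratios were 0.68, 0.76 and 0.86, against 0.65, 0.75 and 0.85 in theory.

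**The case against.** The strongest reply is that nothing here is wrong. Time, treatment and interaction is a standard, unbiased model, the 0.45 SD matches it, and a condensed article may leave baseline handling to an analysis plan. A power calculation without covariates is routine when no correlation is available and does not by itself fix the analysis. The Aim 2 clause also omits covariates that appear elsewhere, so its silence on the baseline biomarker is weak evidence of exclusion.

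Much of this stands. The model is valid, and the power statement alone would not carry the point. But the treatment main effect is not an omission: it is written into the model, and an analysis plan that implements those terms inherits the inefficiency.

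The size is also open to challenge. It depends on an unstated ρ, and the gain is about 4 points at ρ = 0.8. Holding 0.45 SD of change fixed means the underlying difference varies with ρ, from 0.53 SD of a single value at ρ = 0.3 to 0.28 at ρ = 0.8, so the rows of the table describe different absolute effects. Both points are fair. Within each row, however, the two analyses face the same effect, and adjustment wins in every one.

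Finally, the other mechanistic analyses, namely the biomarker-by-treatment interactions on outcome and the Aim 4 growth models, are not touched by this point.

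**Conclusion.** The point holds as a minor, nearly free improvement. As written, the Aim 2 biomarker contrast is a raw difference in change. Conditioning on the baseline already collected would cut its variance by (1−ρ)/2: 35% at ρ = 0.3, 25% at 0.5, 10% at 0.8. For 0.45 SD of change, power rises from 81% to between 85% and 94% over ρ from 0.8 down to 0.3, and the gain is at least 5 points for ρ up to about 0.7.

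This rests on an assumed ρ, two-sided 5%, equal variances and 80 complete pairs per arm. With missing follow-up the mixed-model estimate is no longer exactly the simple difference in change, but the free baseline difference remains.

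The margin is thin: 78 per arm needed, 80 planned, and the attrition figures in Sample size {14} cover recurrence only. The Discussion reports that in-lab biomarker assessments were halted in March 2020 with 26 participants in active treatment. Purely as an illustration, if all 26 lacked a post-treatment value, evenly split, (160 − 26)/2 = 67 per arm would give 73% power as planned, against 85% with adjustment at ρ = 0.5 and 80% at ρ = 0.7.

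The primary recurrence analysis is unaffected.

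**What to change.** In Aim 2, keep the mixed model but constrain the arms to a common pre-treatment mean: time effects plus treatment-by-time terms at the post-baseline visits, with no treatment main effect. Alternatively, use ANCOVA on the post-treatment biomarker with its pre-treatment value as covariate. The constrained mixed model has the advantage of keeping participants who lack a pre-treatment measurement, whom ANCOVA without imputation would drop. Include the three randomisation strata, so that the analysis reflects the stratified allocation; no gain from the strata is counted in the figures above.

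In Sample size {14}, restate the 0.45 SD for that model, naming the scale (SD of change or of a post-treatment value) and the assumed pre-post correlation, preferably with a range.

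The cost is one line of model specification and no new data. The one real drawback is that the power statement then depends on a correlation that has to be justified.
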